#### 8.1.3 Secondary outcomes

##### Secondary outcomes

To demonstrate that the combined treatment improves:

- non-invasive outcomes of NAFLD, i.e. multiparametric MRI of liver and surrounding subcutaneous adipose tissue (MRI-PDFF, MR elastography, corrected T1), FibroScan Elastography and Controlled Attenuation Parameters, and plasma panel Enhanced Liver Fibrosis (ELF) panel, pro-C3.
- change in blood markers from baseline to end of treatment, namely: liver enzymes (i.e. alanine amino transferase (ALT), aspartate amino transferase (AST), gamma glutamyl transferase (GGT), alkaline phosphatase (ALP)), inflammatory blood markers (i.e. leukocytes, monocytes, CRP, IL-1( $\beta$ ), IL-6, IL-11, IL-17, IL-32, TNF- $\alpha$ , IFN- $\gamma$ , additional markers of inflammatory pathways), SCFA (i.e. propionate, butyrate, acetate), lactate, ethanol, plasma lipids (i.e. LDL, HDL, triglycerides, total cholesterol), FGF-21, adiponectin, leptin, lipopolysaccharides, zonulin, estrogen, vitamin B12, folate acid, other metabolomic and lipodomic outcomes.
- microbiome read outs (composition, engraftment, strain tracking) en metabolites, fecal SCFA-composition, and fecal albumine
- glycemic control, insulin resistance, body weight/BMI, waist circumference and percentage body fat
- MetSy criteria / %
- SCFA production and GLP1 gene and protein expression indicating GLP-1 production
- liver gene expression profile: lipogenic, inflammatory and fibrogenic pathways
- liver pathology, histopathological features, immunofluorescence and assessment of pathophysiological proteins

- NAFLD histology as assessed with a deep-learned algorithm scoring whole slide images of liver biopsies.
- 
- Continuous glucose monitoring (4x 7 consecutive days)
- quality of life (general (SF36) and NAFLD/NASH-specific (CDLQ-NAFLD)).

#### **8.1.4 Other study parameters**

- Sex
- Age
- Ethnicity
- Height
- Weight
- BMI
- Waist circumference
- Percentage body fat
- Comorbidities (e.g. diabetes)
- Smoking, yes/no
- Alcohol intake
- Polypharmacy (defined as chronic use of  $\geq 5$  different medications)
- Daily caloric intake
- Daily fat and sugar consumption

### **8.2 Randomisation, blinding and treatment allocation**

Double blind, 1:1 to receive synbiotic treatment in combination with LFMT capsules or placebo. Groups will be stratified by proton-pump inhibitor use, metformin use, and histopathological fibrosis score.

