### 4.2 Inclusion criteria

#### *Patients*

- age 18-75 years
- biopsy-proven NASH obtained up to 32 weeks before screening: SAF Steatosis score  $\geq 1$ , Activity  $\geq 2$ , Fibrosis  $< 4$ ; 50% of participants should at least have NASH fibrosis stage 1, 2 or 3 according to the NASH CRN fibrosis staging system based on tandem reading of two expert liver pathologists
- fluency in Dutch or English
- participants should be able to understand the information and give informed consent

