#### 4.4 Sample size calculation

Based on our FMT pilot study  and the study of *A. soehngenii* in MetSy (average GLP1 increase: 42%), taking into account the additional potential benefits of the synbiotic treatment approach, we performed a power analysis to calculate the number of participants necessary to detect a 25% reduction in our primary outcome parameter, reversal of steatosis and necro-inflammation following donor FMT combined with the synbiotic treatment. For a desired alpha of 0.05 and a desired power of 0.8, a sample size of 24 participants/arm will be required, ergo 48 total.

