## 8. METHODS

### 8.1 Study parameters/endpoints

#### 8.1.1 Main study parameter/endpoint

#### 8.1.2 Primary outcome

To demonstrate that *A. soehngenii* combined with pasteurized *A. muciniphila* and *B. animalis* subsp. *lactis*, FOS and conditioned vegan FMT reduces NASH as defined by an improvement of liver histology in individuals with NASH and fibrosis stage 0-3, with improvement defined as reduction of steatohepatitis by  $\geq 1$  SAF-A point and no worsening of liver fibrosis, or improvement in  $\geq 1$  stage liver fibrosis and no worsening of steatohepatitis.

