## 10. STATISTICAL ANALYSIS

Statistical analyses will be performed by SPSS statistical analysis software and R-studio.

Normality of the data will be assessed by a Kolmogorov–Smirnov test. Data transformation will be done if the data is not normally distributed. The primary analyses of studied primary parameters will be performed between the baseline and endpoint intervention by analysis of a two-tailed one-sample t-test, or chi-square test. If the data is not normally distributed and data transformation is not possible, the Mann-Whitney test will be used. Further associations will be assessed with Pearson rank correlation test / Pearson chi-square test.

Paired categorical data will be analyzed with McNemars test. Paired continuous data will be analyzed using a paired T-test when normally distributed, and a Wilcoxon signed-rank test when not normally distributed.

Using R, we will use statistical packages that employ machine-learning algorithms to reveal which metabolites and microbiota best predict favourable response. An Elastic Net machine learning classification algorithm in combination with a stability selection procedure will be used to identify biological features that change differently between the two treatment groups. Also using R, a deep-learned algorithm scoring whole slide images of liver biopsies will be applied and analyzed.

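### Randomisation is stratified by three factors, but Section 10 names only unadjusted tests, never uses baseline as a covariate, and relies on paired tests that do not compare the arms

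*Protocol*

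**What the plan says.** Protocol Section 8.2 sets the allocation: "Double blind, 1:1 to receive synbiotic treatment in combination with LFMT capsules or placebo", followed by "Groups will be stratified by proton-pump inhibitor use, metformin use, and histopathological fibrosis score". The Summary repeats the three factors. Neither place gives the number of fibrosis levels, the block size or the allocation method.

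Eligible patients are "individuals with NASH and fibrosis stage 0-3" (Section 8.1.2). Section 4.2 adds a quota: "50% of participants should at least have NASH fibrosis stage 1, 2 or 3 according to the NASH CRN fibrosis staging system". The total is 48 patients, 24 per arm (Section 4.4).

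Section 10 names these tests:
- For the primary parameters: a two-sided one-sample t-test or a chi-square test, applied between baseline and endpoint, with Mann-Whitney as the fallback for non-normal data.
- For paired categories: McNemar's test.
- For the rest: "Paired continuous data will be analyzed using a paired T-test when normally distributed, and a Wilcoxon signed-rank test when not normally distributed".
- As the gate between these: "Normality of the data will be assessed by a Kolmogorov–Smirnov test".

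No stratification factor and no baseline covariate appears in any of them. Baseline is used, but as change: in the responder definition (Section 8.1.2), in the blood-marker outcomes (Section 8.1.3) and in the baseline-to-endpoint comparison of Section 10.

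**The concern.** Three things do not fit together.

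First, the design balances the arms on fibrosis score, yet the named analysis ignores it. Fibrosis is tied to the endpoint by construction. Response can come through activity or through a drop of one fibrosis stage, and a patient at F0 cannot use the second route. If a stratification factor is prognostic and the test ignores it, the test is conservative and loses some power.

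Second, the paired tests answer a different question from the trial's. Every patient takes the synbiotic, and Section 11.3 expects it to help in both arms. A significant paired test in the LFMT arm, or in both arms, says nothing about what LFMT adds.

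Third, for outcomes measured at baseline and week 24 (MRI-PDFF, liver enzymes, stiffness, weight), change alone uses baseline less efficiently than ANCOVA does. With 24 patients per arm and two biopsies each, efficiency that costs nothing is worth having.

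**Working it through.** **The plan's own figure.** Section 4.4 gives 24 per arm to detect a 25% reduction at alpha 0.05 and power 0.80. It states no control rate and no SD, so it cannot be reproduced. Nothing below depends on it except the total of 48.

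**1. What a paired test estimates.** Let s be the synbiotic effect, t the change over time (including regression to the mean, since entry requires SAF activity of at least 2), and f the LFMT effect.
- Expected change, placebo arm: s + t
- Expected change, LFMT arm: s + t + f
- Paired test in the LFMT arm: tests s + t + f = 0
- Paired test on both arms pooled 1:1: tests s + t + f/2 = 0
- Between-arm difference: (s + t + f) − (s + t) = f

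Only the last isolates f. This step needs no assumed number.

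**2. Primary endpoint: unadjusted chi-square versus CMH stratified by F0 versus F1–F3.** Assumed: 12 patients per arm in each fibrosis group (48 patients, 1:1, half F0), two-sided 5%, 200,000 simulated trials. Control response rates and the odds ratio (OR) are assumptions, because the protocol gives none. The CMH statistic is [Σ(a − t/2)]² / ΣV with V = 12·12·t·(24 − t)/(24²·23), where a is the number of LFMT responders and t all responders in the stratum, without continuity correction.

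| Control response in the two groups | Type I error, chi-square | Type I error, CMH | Power at OR 6, chi-square | Power at OR 6, CMH |
|---|---|---|---|---|
| 10% / 50% | 3.0% | 4.9% | 69% | 74% |
| 20% / 50% | 4.1% | 4.8% | 80.4% | 81.4% |
| 20% / 40% | 4.5% | 4.8% | 84.2% | 84.4% |
| 30% / 30% | 5.1% | 4.9% | 87% | 87% |

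In the first row, OR 6 turns 10% into 40% and 50% into 86%, so overall response is about 30% versus 63%. That is a large effect. The gain is 5–6 points there, about 1 point or less in the next two rows, and nil when fibrosis is not prognostic.

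Two cautions apply. With a continuity correction, CMH power in the first row falls to 61%, below the unadjusted test. In related simulations, CMH over all 16 cells changed power by −8 to +2 points against the unadjusted test.

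**3. Continuous secondary outcomes: ANCOVA versus change score.** With equal variance σ² at both times and correlation r:
- change score variance: 2σ²(1 − r)
- ANCOVA variance: σ²(1 − r²)
- ratio: (1 − r²) / [2(1 − r)] = (1 + r)/2

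At r = 0.5 the ratio is 0.75, so 18 per arm would do the work of 24. At r = 0.7 it is 0.85, or 20.4 per arm. A between-arm change-score test with 80% power would have about 90% and 86% power respectively with ANCOVA. The protocol does not give r.

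**4. Number of cells.** PPI use (2) × metformin use (2) × fibrosis levels:
- four stages: 2 × 2 × 4 = 16 cells, 48/16 = 3 patients each on average
- F0 versus F1–F3: 2 × 2 × 2 = 8 cells, 48/8 = 6 each

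Assumed for the simulation: permuted blocks of 4, PPI use 40%, metformin use 40%; F0–F3 at 35/25/25/15% for 16 cells, and a 50/50 split for 8 cells.

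| Scheme | SD of arm-size difference | Chance of a difference of 6 or more |
|---|---|---|
| 16 cells | 3.7 | 17% |
| 8 cells | 2.6 | 5% |
| Simple randomisation | – | 47% |

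With 16 cells, about 10 hold fewer than 4 patients.

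**The case against.** The strongest reply is that covariates, fibrosis levels and block sizes are ordinary content for an SAP or a randomisation document, so their absence proves nothing. That stands for the levels and blocks. It does not fully answer the tests: Section 10 goes beyond silence and names unadjusted ones, so an adjusted SAP would depart from the protocol.

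It can also be said that fibrosis need not be strongly prognostic. Response is an either/or composite and everyone enters with activity of at least 2, so the activity route is open to all. This stands, and it is why the primary-endpoint gain is conditional. An unadjusted chi-square between arms would be conservative, not invalid.

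Four stronger readings are tempting, and the documents do not support them:
- *The design has 16 cells.* Section 8.2 gives no levels. F0 versus F1–F3 may already be intended.
- *The stratification destroys balance.* No block size or method is stated. Even 16 cells with blocks of 4 do far better than simple randomisation (17% against 47%).
- *Baseline is not used.* It is used, as change from baseline.
- *Section 10 contains no arm comparison.* It names Mann-Whitney as a fallback, a chi-square that could be applied between arms, and an Elastic Net for features that change differently by treatment group. It also does not expressly assign each secondary outcome to a paired test.

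**Conclusion.** The point holds as a mismatch between design and analysis. The named tests ignore all three stratification factors, baseline is never a covariate, and the paired tests cannot isolate the LFMT effect when both arms receive the synbiotic. That last part rests on the protocol alone.

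The efficiency gains rest on assumptions. The firmer one is ANCOVA for continuous secondary outcomes, at 15–25% lower variance for r of 0.7–0.5. For the primary endpoint the gain is 5–6 power points only if fibrosis is strongly prognostic, and otherwise about 1 point or less. The cell count is a point to clarify: if four stages are used, grouping them would cut the chance of an arm-size difference of 6 or more from about 17% to 5%, with blocks of 4 assumed. This is a worthwhile improvement to the analysis. It does not show that the trial's type I error is inflated.

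**What to change.** In Section 10:
- Make the primary analysis a between-arm comparison of responders by a CMH test stratified by F0 versus F1–F3, without continuity correction. Do not stratify it over all cells of the three factors.
- Analyse continuous secondary outcomes measured at baseline and week 24 by ANCOVA of the week-24 value on arm, baseline value and fibrosis stratum.
- Keep McNemar, paired t and Wilcoxon signed-rank tests as descriptive within-arm summaries only.

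In Section 8.2, state the fibrosis levels used for stratification. If they are currently the four stages, use F0 versus F1–F3 for patients not yet randomised; this is the split the 50% quota in Section 4.2 already uses.

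The cost is a change of wording in two sections and, if recruitment is still open and four stages are in use, a small change to the randomisation list. No extra patients, visits or measurements are needed.

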### **8.3 Study procedures**

Individuals with NASH will be recruited from our outpatient clinic.

#### *Screening liver biopsy*

Percutaneous liver biopsies will be performed as a part of screening when individuals are theoretically eligible for participation, unless a liver biopsy has been performed in the previous 36 weeks. A tandem-read by two liver pathologists blinded to any other result will determine if patients will be included in the study.

After the screening is completed, participants will be telephoned with further instructions. Individuals will have a total of one screening and four study visits, and time invested will approximately be 24 hours per person.

#### *LFMT capsules and synbiotics*

Participants will visit the study center at baseline (week 0), week 8, 16, and 24. The study visits will be 8 weeks apart, although a margin of -3 days to +3 days is implemented to take participants schedule and availability into account. On the first three visits, participants will ingest 21 LFMT capsules (or placebo) containing approximately 235mg of lyophilized FMT (this equals 1500mg of fresh FMT) each. In addition, participants will ingest 2 LFMT capsules (or placebo) daily for the duration of the study (24 weeks).

From the baseline visit until the end of the study (24 weeks later), patients will daily take 5 g FOS (powder).

Starting on baseline visit, all participants will also take daily doses of  $10^9$  *A. soehngenii* CH-106 cells (dosage based on previous studies including toxicology study),  $10^{10}$  *B. animalis* subsp. *lactis* BLC1 (a well-studied strain marketed as a probiotic by Sacco SRL) and  $3 \times 10^{10}$  pasteurized *A. muciniphila* ATCC BAA-835T cells (dose based on EFSA approval and obtained from A-Mansia Biotech) for the whole 24 weeks. We have previously observed that gut microbiota composition in the recipient is affected up to 8-12 weeks after donor FMT, so this time window ensures a stable donor gut microbiota composition during the study.

#### *Physical examination*

At baseline and after 24 weeks, we will collect anthropometric data (e.g. body weight, height, waist circumference, bioelectrical impedance etc.).

#### *Fecal samples*

In addition, feces will be collected at baseline, and after 2, 8, 10, 16, 18 and 24 weeks for extensive microbiota analysis and intestinal barrier function assessment.

#### *Blood withdrawal*

Blood will be collected at baseline, 8, 16 and 24 weeks. At baseline and 24 weeks, blood will be investigated on common liver enzymes, indicators of glycemic control, lipids, and general and more NASH-specific parameters. Blood withdrawal on 8 and 16 week is for safety and in a lesser extent for study purposes (e.g. enhanced liver fibrosis-panel).

#### *Liver biopsy (after 24 weeks)*

At 24 weeks, another liver biopsy will be performed to examine the effect of the FMT. The NASH-CRN classification will be assessed on H&E slides, for steatosis, inflammation and ballooning, and with a Sirius red–stained slide for evaluation of fibrosis. RNA for RNA-sequencing will be isolated. Differential gene expression will be assessed over time (baseline and 24 weeks) and by treatment allocation (vegan donor FMT versus placebo).

#### *MRI and Fibroscan*

In addition, before baseline and at 24 weeks. a multiparametric MRI of the liver and MRI of visceral and subcutaneous fat will be performed with a 3T Philips Ingenia MRI scanner. Participants will be screened for contra-indications for MRI prior to inclusion in this study. Participants will be provided with metal free hospital clothing if necessary. The total scan time will be approximately 45 minutes to estimate visceral and subcutaneous adipose tissue depot volume, hepatic and pancreatic fat content, as well as hepatic fibrosis and inflammation. In addition, a Fibroscan (ultrasound) will be performed to investigate liver stiffness.

#### *Food diary, glucose monitoring and questionnaires*

Participants will, moreover, keep a diary of their daily food intake for 5 days in the week before and after study visits. In addition, they will fill in questionnaires physical endurance and quality of life at baseline and 24 weeks.

Last, continuous glucose measurements will be performed at house using portable devices, during a consecutive period of 1 week (7 days) in the week before baseline, week 1, 9, 17 and 25.

#### 8.4 Figure 8 summarizes the study visits. Withdrawal of individual subjects

[figure not shown]

Figure 8: Overview of study visits

Participants can leave the study at any time for any reason if they wish to do so without any consequences. The investigator can decide to withdraw a participant from the study for urgent medical reasons.

##### 8.4.1 Specific criteria for withdrawal

Participants with any new condition during the study that require hospital admission, change in drug prescriptions or likely to affect the outcome of this study will be withdrawn.

Participants will also be withdrawn if instructions as written in the protocol are not followed.

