#### 8.5 Replacement of individual subjects after withdrawal

Withdrawn participants will be replaced in order to attain the desired sample size.

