#### 8.6 Follow-up of subjects withdrawn from treatment

Withdrawn patients will be followed for SAEs until 6 months after inclusion.

Participants withdrawn for medical reasons will be followed until the interfering condition has resolved or reached a stable state.

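### Mandatory withdrawal after randomisation, replacement, and no efficacy follow-up leave a selected completer set, so the arm comparison is open to bias of unknown size and direction

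*Protocol*

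**What the plan says.** Withdrawal is compulsory under two rules in section 8.4.1. The first concerns a new condition arising during the study. Hospital admission is one trigger, and the sentence continues: "change in drug prescriptions or likely to affect the outcome of this study will be withdrawn". The second concerns adherence: "Participants will also be withdrawn if instructions as written in the protocol are not followed".

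Section 8.5 then states: "Withdrawn participants will be replaced in order to attain the desired sample size". The desired size is set in section 4.4: "For a desired alpha of 0.05 and a desired power of 0.8, a sample size of 24 participants/arm will be required, ergo 48 total". That section has no allowance for dropout.

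Section 8.6 states: "Withdrawn patients will be followed for SAEs until 6 months after inclusion". It adds that patients withdrawn for medical reasons are followed until the interfering condition resolves or stabilises. It mentions no efficacy assessment.

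The primary outcome (section 8.1.2) is histological improvement, and the biopsy that measures it is taken at 24 weeks (section 8.3). Allocation is described in section 8.2: "Double blind, 1:1 to receive synbiotic treatment in combination with LFMT capsules or placebo".

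**The concern.** Every trigger in section 8.4.1 occurs after randomisation, and one of them is defined by its likely effect on the outcome. A patient withdrawn before week 24 has no planned primary endpoint and is replaced by someone who must pass the same filter. Followed as written, the rules produce 24 patients per arm who adhered to the protocol and had no triggering condition. Randomisation protects the comparison of everyone allocated; it does not protect a comparison of those who remain.

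If the patients who leave differ in prognosis between arms, the observed difference mixes treatment effect with selection. Neither the size nor the direction of that mixture could be checked later, because the histology of the patients who left would not have been collected.

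**Working it through.** **The plan's own figure.** Section 4.4 gives 24 per arm to "detect a 25% reduction in our primary outcome parameter". It states no control rate or standard deviation, and does not say whether the 25% is absolute or relative, so the number cannot be reproduced. Read as 25 percentage points on the binary endpoint, two-sided without continuity correction, n is 27 to 62 per arm depending on the control rate. As a comparison of means, 24 per arm needs an unstated SD of about 0.305 for a difference of 0.25. What follows uses only the 24 per arm and the two-sided chi-square option of section 10 ("two-tailed one-sample t-test, or chi-square test").

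**Inputs.** The protocol gives 24 completers per arm, alpha 0.05 and 1:1 allocation. The response and withdrawal rates below are assumptions, because the protocol states none. True response is p = 0.35 in both arms, so there is no treatment effect.

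**Formula.** Let wR and wN be the probabilities that a responder and a non-responder are withdrawn. Replacement draws from the same population through the same filter, so the response rate among completers in an arm is

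p(1 − wR) / [p(1 − wR) + (1 − p)(1 − wN)].

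The rejection rate is the exact probability, over all outcomes of two binomials of size 24, that the uncorrected chi-square test is significant at 5%. With no selection it is 5.2%.

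| Withdrawal pattern | LFMT completers | Placebo completers | Difference | Rejection |
|---|---|---|---|---|
| Unrelated to response: 20% of LFMT, 5% of placebo | 35.0% | 35.0% | 0 | 5.2% |
| Same link in both arms: 20% of non-responders, 5% of responders | 39.0% | 39.0% | 0 | 5.5% |
| 20% of LFMT non-responders, 5% of all others | 0.3325/0.8525 = 39.0% | 35.0% | +4.0 points | 6.3% |
| 30% of LFMT non-responders, 5% of all others | 0.3325/0.7875 = 42.2% | 35.0% | +7.2 points | 8.7% |
| 20% of the LFMT arm, all non-responders; none on placebo | 0.35/0.80 = 43.75% | 35.0% | +8.75 points | 10.2% |
| 30% of the LFMT arm, all non-responders; none on placebo | 0.35/0.70 = 50.0% | 35.0% | +15 points | 19.9% |
| 30% of LFMT responders, 5% of all others | 0.245/0.8625 = 28.4% | 35.0% | −6.6 points | 8.0% |

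The two extreme rows remove 0.20/0.65 = 31% and 0.30/0.65 = 46% of LFMT non-responders and nobody else. They are the limit for those withdrawal rates when no placebo patient leaves.

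**Effect of replacement.** In the +4.0 row, 14.75% of the LFMT arm and 5% of the placebo arm leave, so 24/0.8525 + 24/0.95 = 53.4 patients are randomised to obtain 48 completers. The arms are full again and the +4.0 points remain.

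**The case against.** A reader might infer that the comparison is biased, and biased in favour of LFMT. The documents do not support that. With no true effect, the bias is zero when withdrawal is unrelated to response or related to it equally in both arms, and it reverses when LFMT responders leave more often. The trial is double-blind and both arms take the same number of capsules, so pill burden gives no reason for a difference. Section 6.5 reports gastrointestinal symptoms after LFMT capsules as similar to those on placebo. Response is read only at the final biopsy, so nobody can be withdrawn for histological non-response itself. These points stand, and they make the extreme rows unlikely. They do not remove the exposure: blinding limits discretionary removal, but adherence, new conditions and prescription changes can still differ by arm once treatment has begun.

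Two broader readings of section 8.4.1 should also be avoided. The prescription trigger is naturally read as tied to a new condition, so it does not cover every medication change. An adverse event that meets none of the triggers does not lead to withdrawal, so the completers are not free of events.

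It can also be said that analysis sets and missing-data rules belong in a statistical analysis plan, and that section 8.6 is silent on the biopsy but does not forbid it. Both are fair, and the lack of an imputation rule in section 10 is not part of this point. But such a plan could not recover biopsies that were never taken, and replacement is a protocol rule.

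**Conclusion.** The point holds as a stated design rule that leaves the primary comparison open to bias of unknown size and direction. Sections 8.4.1, 8.5 and 8.6 together make the 48 counted patients a selected completer set, and replacement does not repair this. On the assumed 35% response, plausible differential patterns shift the difference by about 4 to 7 points and raise the false-positive rate from 5.2% to between 6.3% and 8.7%. The shifts of 9 and 15 points (10.2% and 19.9%) are extremes and should not be quoted as expected values. All these sizes rest on assumed withdrawal rates; the finding itself rests on the wording of the three sections. It should be fixed before patients are withdrawn, because missed week-24 biopsies cannot be recovered.

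**What to change.** - **Sections 8.4.1 and 8.6:** separate stopping study treatment from leaving the study. The clinical criteria for stopping remain the sponsor's decision. Keep the already planned week-24 visit and biopsy for every randomised patient who still consents and for whom the investigator judges it safe.
- **Section 8.5:** additional patients may be enrolled, but none displaces a randomised patient from the analysis. The alternative is to randomise more at the outset. With an assumed loss d, 48/(1 − d) gives 54 at 10%, 60 at 20% and 69 at 30% (70 to keep 1:1). This restores the count only.
- **Primary comparison:** include all randomised patients by allocated arm, with the rule for missing biopsies fixed before unblinding. The present section 8.4.1 criteria then define a per-protocol sensitivity set only.

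**Cost.** A protocol amendment, a second biopsy for some patients who have stopped treatment, and some dilution of the effect by non-adherent patients. Missing biopsies also cost power, and how much depends on the rule chosen. For example, take an assumed 35% versus 60% response with 24 per arm. If 20% of biopsies are missing in each arm and counted as non-response, the rates become 28% and 48%, and exact power falls from 45% to 31%. That argues for keeping as many week-24 biopsies as possible and choosing the missing-data rule with care.
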